#### Stratification and Randomization

In a first step, participants displaying T-values of the FEEL-KJ Total score outside the clinical norm (T-value <40 or >60 in accordance with the transdiagnostic inclusion criterion of substantial emotion dysregulation) and in addition fulfilling the primary diagnosis of either a depressive, anxiety or conduct disorder, will be included in the study. Secondary diagnosis, especially comorbid disorders related to another subgroup of the current trial (e.g., primary diagnosis: depression and secondary diagnosis: anxiety) will be recorded and taken into consideration for the analysis. Age and sex will serve as stratification variables allocating 12 participants of each clinical group to one age block (age block1: 13 + 14 years; age block 2: 15 + 16 years; age block 3: 17 + 18 years) with half of the participants per age block being female and the other half male.

In a second step, a block randomization is performed: 50% of the participants of each block of each subgroup will be randomly allocated to the real or sham tDCS group, respectively (18 of 36 for each of the three clinical groups, female: male = 1:1). This results in 54 subjects per experimental condition (balanced related to clinical groups, age and sex; see Figure 1).

**Figure 1 F1:**
[figure not shown]
Overview of stratification and randomization of clinical groups.

#### Blinding

For this triple-blind study, the protocols for every participant will be preset using a 4-digit code, which the stimulation device encodes as sham or real stimulation. Neither the participant, nor the study team (investigator, psychologists, physicians) will know which kind of stimulation is applied and will therefore be blind to the type of intervention (sham vs. real). Regarding the analysis of the main hypotheses, also the data analysts will be blinded regarding the experimental group assignment (triple-blind procedure). The blinding and code storage will be done by a staff member not directly involved in the intervention and the day-to-day management of the study. To investigate the success of the blinding, participants and their caregiver and the study team, will be asked about their beliefs of the received stimulation type at the end of the stimulation.

#### Inclusion and Exclusion Criteria

##### Inclusion Criteria

Participants eligible for this clinical intervention study must meet the following criteria^1^:

male and female adolescents from 13 to 18 yearswith substantial deficits in emotion regulation (T-value <40 or >60 of the FEEL-KJ)fulfilling the primary diagnosis of either a depressive disorder (F32, F33), a conduct disorder (F91, F60.2) or an anxiety disorder (F40.1, F41.1) according to the Clinical Description and Diagnostic Guidelines of the ICD 10 (75)IQ > 70 (i.e., exclusion of profound, severe, moderate, and mild intellectual disability) on a state-of the art IQ inventory [e.g., WISC/WAIS (76, 77)].informed consent and the ability to understand the study information and instructions (sufficient knowledge of German) - signed declarations of consent/assent of study participant and of parent/legal guardian.

##### Exclusion Criteria

all MRI contraindications such as non-removable metallic devices (cardiac pacemakers, defibrillator, cochlear implant, intracranial/cranial stimulators and other metals, any implant or stainless-steel graft)epilepsy or related seizure disorders,other severe neurologic diseases or medical conditions (such as chronic migraine, skull defect, craniotomy)acute suicidalitycontinuous benzodiazepine medication^2^concomitant neurofeedback, stimulation intervention or participation in other clinical trialsfailure to comply with the study protocol or to follow the instructions of the investigating team.

### Procedure and Intervention

After study inclusion, stratification and randomization, pre-measures including psychological questionnaires (first visit date), behavioral tests (second visit date) and fMRI paradigms (third visit date) will be conducted. Then, one of the two brain stimulation interventions (real or sham stimulation) will be conducted with each of the participants. In the beginning of every session, the participants will sit down on a chair and complete a brief questionnaire about their general wellbeing, attention, motivation and other life aspects (short mood questionnaires). Afterwards, an electrode stimulation cap will be placed on the head of the participant. Then, the treatment condition is initiated: either real transcranial direct current stimulation (experimental group) or sham (placebo) stimulation (control group). Both brain stimulation interventions will comprise 10 sessions on consecutive days (except weekends), as it was previously done in different successful tDCS treatment trials [summarized in (39)]. After the interventions, the same tasks as for the pre-measurement will be conducted for post-measurements. Follow-up measures, one, respectively, 3 months after the stimulation intervention, will similarly include all tasks as the pre-/ post measurement, except MRI measures.

#### Electrode Placement and Current Strength

Due to the inter-individual variability in the response to tDCS in adult studies (79, 80) as well as the specific features of the stimulation-generated electric fields' behavior in the youth population (81), a suggestion in the pediatric tDCS literature for simulation-based stimulation protocols has been brought up (53, 58). MRI-based finite-element models of the human head can assist parameter choice and dose individualization through the estimation of the spatial distribution and the magnitude of the electric fields (82). In children and adolescents, due to the fast changes in the anatomical characteristics (gray matter alterations, bone thickness, cortical-spinal fluid quantity), field magnitudes are usually 1.5–2 times higher than in the adults (83, 84).

Therefore, in this clinical trial, in an attempt to increase spatial precision in targeting the non-superficial cortical area of the vmPFC, an optimized high definition, multi-channel montage based on computational simulations, was chosen. For this reason, the optimization was conducted with the Stimweaver algorithm (Stimweaver montage optimization service from Neuroelectrics NE, Barcelona) to determine the positions of the computed 8 electrodes and required currents for the vmPFC (Figure 2). Based on two head models (male/female) generated from structural T1 images from adolescents within the same age range from a previous clinical trial ran by our research group, an optimized montage for female and male participants was calculated. For female participants anodal stimulation will include electrode positions FP1, FP2, FPz, and P08, while cathodal electrodes will be placed at electrode positions FC1, FC2, and Fz. For male participants anodal stimulation will include electrode positions FP1, FP2, and O1, while cathodal electrodes will be placed at electrode positions FC1, FC2, Fz, and F4. The maximal injected current into the brain at any given time will be below 2.00 mA and maximum current at any electrode is 1.00 mA. The electrodes used in this study are 1 cm radius Ag/AgCl cylindrical electrodes with conductive gel underneath (NG PiStim electrodes).

**Figure 2 F2:**
[figure not shown]
Electric field distributions on gray matter with current intensities within the established safety range for adolescents, generated by the optimized montages for vmPFC from Neuroelectrics. First row: female frontal brain view, second row: male frontal brain view.

#### Stimulation Protocol and Intervention Procedure

True anodal tDCS will be applied to the experimental group for 20 min. In the first minute, current will fade-in for 30 s to 2 mA and this current intensity will be maintained. In the 20th minute, tDCS will be reduced and fade-out in the last 30 s. During the sham stimulation in the control group, a fade-in phase for 30 s will be applied, followed by 15 s of 2 mA stimulation and then a fade-out phase for 30 s. Here, participants experience the typical skin sensation during the beginning and thereby will remain unaware of the real condition (85, 86).

The planned 60 min for each session include 20 min of preparation, 20 min of stimulation (real or sham) and 20 min of debriefing. During the 20 min of stimulation, two aspects of practical importance are covered: Firstly, the adolescents should experience the time during brain stimulation as pleasant, appealing and entertaining. Secondly, the longer-lasting effects of tDCS have previously been shown to depend on the emotional and physiological state during tDCS administration (87). Both aspects will be addressed by the following structured intervention procedure: (A) At the beginning of the stimulation, five min of the first part of a child-friendly movie (88) focusing on emotions will be presented to the participants. (B) To further trigger brain areas involved in emotion processing, participants will be asked to assess the emotions of different faces, presented in a naturalistic [videos from EU Emotion Stimuli Set (89) and morphing [clips from FACES Database, (90)] mode (Emotion Recognition Task, ERT). (C) After this expected basic pre-activation of areas involved in general emotion recognition, the complex interplay and link between brain areas involved in emotional functioning (limbic areas, e.g., amygdala) and in parallel brain areas involved in cognitive functioning (e.g., PFC) are aimed to be triggered in parallel by a working memory n-back task with emotional face stimuli (emotional n-back task, e- nBACK). (D) At the end of the stimulation, the next part of the movie will be presented. With this structured intervention procedure, both preconditions for an efficient brain stimulation therapy in adolescents are addressed: the entertaining, as well as the brain-activating function. Further, the randomized and adaptive character of the applied stimuli will, together with the presentation of the full movie (divided into 10 sessions), facilitate focused engagement of the participants during the repeated stimulation sessions and standardize the activity during the stimulation across all participants. Additionally, study motivation in form of sugar-free candies, small give-aways and vouchers from cooperating institutions will be given to the participants at the end of each session.

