##### Emotional n-back Task

Cognitive and emotional capacities will be investigated using a modified version of a working memory n-back task (117) with emotional face stimuli pre and post brain stimulation intervention. This paradigm was developed as a modified emotional n-back task, which adopts to the current performance of the patient, varying the degree of difficulty adaptively during each stimulation session. During the task, behavioral reactions such as button presses (correct/ incorrect classification, omission) and reaction times will be recorded.

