##### Emotion Recognition Task

Emotions of different static and morphing faces displaying different emotional states will be presented to the participants to investigate the perception of emotions in others. The emotional stimuli will be taken from validated Databases [EU Emotion Stimuli Set (89); FACES Database (90)], and will be presented at pre and post measures. Besides behavioral reactions (correct/ incorrect classification, omission, reaction times), also gaze behavior, fixation duration and pupil dilation will be recorded via eye tracking system (Tobii Group, Danderyd, Schweden).

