### Outcomes

The primary outcome of this study is the change in emotion regulation ability, measured by the raw score of the FEEL-KJ (74). Here, we expect an increase in emotion regulation after the intervention of the experimental group in total (as well as for each clinical experimental subgroup) compared to the control group in total (as well as for each clinical control subgroup).

As exploratory outcomes, we will investigate if the application of tDCS improves the disorder-related clinical symptomatology, quality of life or emotion regulation, whereas changes in raw scores of the related self- and parental reports (as summarized in Psychological Self- and Parental Ratings) are defined as secondary endpoints.

Further we will explore if indices of emotion recognition [measured via Frankfurter Test and Training for Recognizing Facial Affect (FEFA II) and the Emotion Recognition Task (ERT)], and (implicit) emotion regulation (measured via eSTROOP) improve from before to after tDCS stimulation. In addition, measures of attentional bias [*via* Attentional Bias Task (ABT)] and working memory (*via* e n-BACK) will give insight regarding potential improvements in the related indices from before to after tDCS stimulation. Indices of each task (such as the number of correct behavioral assignments, commission, omission, reaction times, eye gaze fixation duration, pupil dilation, brain activation, brain connectivity) are summarized in Eye Tracking and Behavioral Measures and fMRI Procedure and Measures.

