Here, specific training effects have to be considered regarding potential biases in outcome measures. Both treatment groups undergo the described emotion regulation training, regardless of receiving real or sham stimulation. Therefore, we will not be able to reduce our results to the pure effect of the activation via tDCS since an induced modulatory training effect is actually desired. Moreover, the emotion regulation training itself might lead to improvements in both groups. If group differences in the improvements of the clinical outcome measures become insignificant, future research will be needed to differentiate between the training and stimulation influences. Only after this analysis, it is possible to clarify if only the developed emotion-cognition training procedure alone is sufficient for an effective training or if the brain stimulation further increases the therapeutic effect. In this case, also the influence of the engagement in the study *per se* would need to be investigated via a suitable control condition.

As the here presented clinical therapy trial not only includes three groups of patients and a novel brain stimulation procedure, but also pre- and post-measures on multiple levels (subjective psychological measures via self- and parent-rated questionnaires, behavioral and eye tracking tests, neuronal measures via MRI), inclusions of further diverging control groups would have gone beyond the scope of this single study.

Considering the developmental psychophysiological perspective, this project does not only highlight the treatment advantages of the excitability of the adolescent brain, it also takes the chance to possibly intervene early enough to hinder a further worsening of the clinical symptoms of depressive, anxiety or conduct disorders and the pathological manifestations in adulthood.

Utilizing a transdiagnostic approach for the treatment of emotion dysregulation as a common factor in anxiety, depressive and conduct disorders, this study is oriented toward a dimensional perspective on mental health as it was formalized in the Research Domain Criteria framework. If successful, this project will provide a non-invasive therapeutic option for the most prevalent psychiatric disorders in adolescents, with the possibility to transfer the protocol to related conditions in future studies.

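### The Emotion Recognition Task and emotional n-back are practised during stimulation and then reused as outcomes, so a real-versus-sham difference on them cannot alone show better general functioning

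*Protocol article*

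**What the plan says.** **Training.** The section Stimulation Protocol and Intervention Procedure describes four steps within the 20 minutes of stimulation. In step B "participants will be asked to assess the emotions of different faces, presented in a naturalistic [videos from EU Emotion Stimuli Set (89) and morphing" formats are used, the latter being "clips from FACES Database, (90)] mode (Emotion Recognition Task, ERT". In step C, emotional and cognitive brain areas are to be "triggered in parallel by a working memory n-back task with emotional face stimuli". The Emotional n-back Task section adds that this paradigm adjusts to the patient, "varying the degree of difficulty adaptively during each stimulation session". On the number of sessions, Procedure and Intervention says: "Both brain stimulation interventions will comprise 10 sessions on consecutive days (except weekends".

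**Assessment.** The Emotion Recognition Task section gives the ERT at pre and post. Of its source it says: "The emotional stimuli will be taken from validated Databases [EU Emotion Stimuli Set (89); FACES Database (90". The emotional n-back is also given pre and post. Both tasks have a scanner version (fMRI Procedure and Measures), and all tasks except MRI are repeated at follow-up.

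**Reading of the results.** Outcomes treats emotion recognition as "measured via Frankfurter Test and Training for Recognizing Facial Affect (FEFA II) and the Emotion Recognition Task (ERT", and working memory as measured by the emotional n-back. It asks whether the indices improve from before to after stimulation. The Secondary Hypotheses expect improvement in emotion recognition and working memory in the real arm compared with sham.

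**Caveat already given.** The Discussion says that "specific training effects have to be considered regarding potential biases in outcome measures". It notes that both arms receive the training and that the results cannot be reduced to a pure stimulation effect.

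**The concern.** An outcome meant to show that a general ability has changed is usually a task that the intervention did not rehearse. Here two outcome tasks are rehearsed repeatedly, and they are rehearsed while the current is on. The trial's own rationale is that stimulation should strengthen what is trained at the same time. The result to be expected if the method works is therefore better performance on the practised tasks, and that can happen without any gain in recognising emotions or holding information in mind elsewhere.

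At stake is what a positive secondary result would mean. A difference on the ERT or the emotional n-back could be reported as improved emotion recognition or working memory when the data show only that the practised task was learned faster. The before-to-after wording in Outcomes adds a second risk: a reader or author may interpret the change within the real arm, where ordinary practice is included in full.

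**Working it through.** The plan gives no figure on this point. Its sample size concerns the FEEL-KJ, and nothing below depends on it. The check has two parts.

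**1. Trained tasks against outcome tasks**

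| Measure | In the sessions | At assessment | Read as |
|---|---|---|---|
| ERT | Videos and morphing clips; EU Emotion Stimuli Set and FACES | Static and morphing faces; same two databases. Scanner: morphing only | Emotion recognition |
| Emotional n-back | Adaptive difficulty | Pre and post. Scanner: 0-back and 2-back | Working memory |
| FEFA II | Not listed | Pre and post | Emotion recognition |
| Emotional Stroop | Not listed | Pre and post, and scanner | Implicit emotion regulation |
| Attentional Bias Task | Not listed | Pre and post | Attentional bias |

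Two of the five behavioural tasks are trained, as are two of the three fMRI task paradigms (ERT and n-back, not the Stroop). Emotion recognition keeps one untrained behavioural measure, the FEFA II. Working memory has none.

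**2. What the randomised comparison can and cannot separate**

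Let P be the mean practice gain under sham, k the proportion by which stimulation speeds learning of the trained task, and G the effect of stimulation on general functioning, with P and G in SD units.

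- Change in the sham arm: P
- Change in the real arm: P(1 + k) + G
- Real minus sham: kP + G

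P by itself drops out. The product kP does not, and a single observed difference cannot divide itself between kP and G.

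A simulation with G = 0 illustrates this. It used 54 per arm as planned, 4,000 runs, and a pre-post correlation of 0.62 borrowed from the FEEL-KJ reliability; the correlation does not affect the mean differences. The values of P and k are assumptions, because the document gives none.

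| P (SD) | k | Change in real arm (SD) | Real minus sham (SD) |
|---|---|---|---|
| 0 | 0 | 0.00 | 0.00 |
| 0.5 | 0 | 0.50 | 0.00 |
| 1.0 | 0 | 1.00 | 0.00 |
| 0.5 | 0.30 | 0.65 | 0.15 |
| 1.0 | 0.30 | 1.30 | 0.30 |

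The simulated differences agree with the formula: 0.30 × 0.5 = 0.15 and 0.30 × 1.0 = 0.30.

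In the rows with k = 0 the sham comparison does its job, although the real arm alone shows a gain of 0.5 to 1.0 SD that has nothing to do with stimulation. That is the hazard of a before-to-after reading. In the last two rows the comparison shows a difference although general functioning has not moved. A difference of 0.30 SD fits equally well with G = 0.30 and k = 0, or with G = 0, k = 0.30 and P = 1.0.

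**The case against.** The strongest reply is that both arms train identically, the hypothesis is real versus sham, and the analysis tests Time by Treatment Condition. Shared practice then causes no bias, as the rows with k = 0 confirm. This stands. A reader might infer that the two tasks measure learning instead of functioning; the documents do not support that. The tasks mix the two.

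The Discussion also concedes training effects and calls a modulatory effect on training desired. That is fair as a statement of mechanism. But it does not say that two of the outcomes are themselves the trained tasks, and it plans only for the case where group differences are not significant. It does not say how a positive difference on a trained task would be read.

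Three further inferences are tempting and not supported:

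- *The same faces are reused.* Only the same two databases are named. The modes overlap for morphing faces but not for videos and static faces, and a condensed article may leave item lists to the full protocol.
- *Practice drives scores to a ceiling.* No accuracy level or practice gain is given, and several indices (reaction time, gaze, pupil dilation, brain activation) are not bounded by accuracy.
- *Adaptive difficulty makes n-back accuracy uninformative.* The text ties adaptation to the stimulation sessions, and the scanner version has fixed load. The form used at the behavioural assessment is not stated, so this is a possibility only.

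The scanner versions also differ in format from the training as described. The scanner ERT, for example, stops at a button press and is followed by a choice among six options. This weakens the overlap without removing it, since the scanner ERT uses only morphing faces, a practised mode.

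**Conclusion.** The concern holds in a limited form. The documents state that the ERT and the emotional n-back are practised under stimulation over the 10 sessions in both arms and then serve as measures of emotion recognition and working memory. A real-versus-sham difference on either task is a valid randomised result about that task. By itself it cannot support the broader secondary hypothesis, because faster learning of the trained task and better general functioning produce the same difference.

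The point is sharpest for working memory, where no untrained measure is listed and where the argument does not depend on which faces are used. For emotion recognition the FEFA II offers a way out.

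The possible size cannot be taken from the document. The range of 0.15 to 0.30 SD rests on assumed practice gains of 0.5 to 1.0 SD and an assumed 30% faster learning, and shows only that such a difference can arise without any general effect.

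A reader might extend this to the trial's main conclusion; that would be wrong. The FEEL-KJ is a questionnaire and is not one of the trained tasks. The affected outcomes are secondary or exploratory. The change is worth making, but the design does not fail without it.

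**What to change.** 1. In Outcomes, label the ERT and the emotional n-back, behavioural and fMRI, as trained-task (near-transfer) outcomes. State that they are interpreted only as real versus sham, and reword the before-to-after phrasing to match.
2. Rest the claim on general emotion recognition on the FEFA II, which is already in the battery and not part of the sessions.
3. Divide the ERT items once into a training set and a held-out set. Use only held-out items at pre, post, follow-up and in the scanner. If the full protocol already does this, one sentence saying so is enough.
4. State that the n-back is scored at fixed load at assessment, as in the existing 0-back/2-back scanner version, and limit its conclusion to the trained task.

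The cost is a one-off preparation of stimulus lists and a few sentences of text, with no added visits or measures. The drawbacks are fewer distinct items for training and a narrower working-memory claim. The item split has to be in place before the first pre-measurement. The labels and the limits on interpretation can still be added later, provided this is done before unblinding.
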